## Methods and design

This protocol conforms to guidelines presented in the Consolidated Standards of Reporting Trials (CONSORT) [33] 2010 statement extension for randomized feasibility studies and clinical trial protocols (see Additional file: Table S1). The intervention component is an uncontrolled open-label feasibility trial (hereafter referred to as “the intervention”), utilizing a pre-test–post-test within-subject design. The overall study design is illustrated in Fig. 1 (below), whereas the stages of the enrollment, interventions, and assessments Table 1 below (The SPIRIT table).

**Fig. 1 Fig1:**
[figure not shown]
Study flow chart for CAH-Y feasibility study. *CAH-Y* Confident, Active and Happy Youth, *NML-C* Nijmegen Motivation List for Chldren, *SCAS-C/P* Spence Children’s Anxiety Scale, Children/Parents, *SMFQ* Short Mood and Feelings Questionnaire

### Spirit table

**Table 1 Tab1:** SPIRIT table for an uncontrolled open-label feasibility testing of physical activity intervention: Confident, Active and Happy Youth

Timepoint	Feasibility test period				
	Enrolment	Allocation	Intervention		Follow-up
	*T1*	0	*Weeks 1–7*	*T2*	*T3 (follow-up)*
Enrolment					
Eligibility screen	X				
Informed consent	X				
*Baseline assessment*	X				
Allocation		X			
Interventions					
*CAH-Y intervention*					
Assessments					
*Actigraph*	X		X	X	X
*Baseline data (demographic, psychiatric)*	X				
*Biometric data (height, weight)*	X			X	X
*Feasibility outcomes*	X		X	X	X
*SCAS-C/P, SMFQ, NML-C*	X			X	X
*Qualitative interview*	X			X	X

*CAH-Y* Confident, Active and Happy Youth, *NML-C* Nijmegen Motivation List for Chldren, *SCAS-C/P* Spence Children’s Anxiety Scale, Children/Parents, *SMFQ* Short Mood and Feelings Questionnaire

#### Intervention (CAH-Y)

The CAH-Y intervention includes two sessions of 50 min per week, for 7 weeks, in total 14 sessions. However, the final session is approximately 3-h long since it includes a nature hike and a conclusion of the program. Several constraints shaped the delivery format in the form of intervention length, intensity, and overall dosage. Thus, the delivery format is a compromise between evidence from behavior change research, organizational considerations, and clinical considerations regarding the logistical and practical burden on youth and parents (e.g., time spent to commute to treatment, time away from school). Importantly, despite these constraints the intended dose of the intended active mechanisms is still likely to be sufficient to have effect (e.g., moderate to vigorous activity, inhibitory learning, building motivation).

The intervention is group-based with up to eight participants in each group. Two therapists lead each group. Groups are divided into a child group and an adolescent group to accommodate maturational differences. Youth aged 8–13 receive the child intervention, whereas youth aged 14–18 receive the adolescent version. Both versions follow the same format and structure and have the same guiding principles and goals. However, the specific activities in CAH-Y 13 and CAH-Y 18 are tailored to the meet the maturational level and interests of the different age groups.

Each session follows the same structure and format (with exception of the last session as noted above). This structure consists of the following: an introduction and warm-up (10 min), main activity (35 min), and a session wrap-up (5 min). The separate sessions have distinct overarching topics and include a variety of activities. Sessions take place in a gym hall, two sessions involve activities in a swimming pool, and the last session is outside.

Concerning the more specific physical activities in the intervention, sessions include a mix of aerobic (e.g., running, jumping, traversing an obstacle course), resistance (e.g., squats, push-ups), and relaxation exercises (e.g., yoga exercises). The goal for each session is a minimum of 30 min spent in moderate to vigorous intensity activity.

Specifically during the introduction and warm-up, the therapists give psychoeducation to the youth regarding the bidirectional interplay between thoughts, feelings, actions, and particularly the role of avoidance and alternative coping strategies. The exercises are designed to stimulate some distress, fear, and/or discomfort, and the therapists couple these feelings and reactions to the introductory psychoeducation and use the exercises as exposure therapy. A supportive and mastery motivational climate facilitates the individuals need for relatedness [25] and a safe space to practice exposure (being observed), provides an optimal environment to help the youth address, and overcome this fear [34]. Thus, the group format allows youth to observe other youth, allowing them to observe that other youth have similar feelings, fears, reactions, behaviors, and responses as themselves, e.g., we sweat when we are physically active, trying out new activities may make us feel anxious but can be done nonetheless. Gaining this knowledge can help normalize the youth’s understanding of both themselves and others. Importantly, group and peer support are identified as an important intervention component to support active lifestyles [35, 36].

In accordance with self-determination theory, the sessions also strive to satisfy the youths’ needs for autonomy (e.g., giving them choices within a menu of activities to do), competence (e.g., adapting exercises to meet the needs/fitness levels of students), and relatedness (e.g., focusing on group cohesion, group cooperation). Importantly in this regard, the sessions do not have a competitive focus, but focus on being supportive, enjoyable, and fun. An overview of the CAH-Y intervention is presented in Table 2.

**Table 2 Tab2:** Description of the intended structure and format of Confident, Active and Happy Youth program. Notes: *Pa* physical activity

Introduction Sessions 1–2	Treatment stage Sessions 3–12	Closing and transitioning Sessions 13–14
**Main theme:** Alliance and motivation Feeling secure in the group Alliance to the group/therapist Motivation to partake	**Main theme:** Challenge and exposure Moderate to vigorous PA From avoidance to exposure Strengthening motivation	**Main theme:** Transitioning to daily life Active “lifestyle” Continue exposure to PA Motivation to continue
Week 1 2 sessions of 50 min	Week 2-6 10 sessions of 50 min 2 sessions weekly	Week 7 1 session of 50 min 1 session of 3

*PA* Physical activity

### Therapists

Group-leaders will have knowledge of mental health disorders, youth development, group-dynamics, and physical activity to adequately understand and be able to meet the needs of the youth. Thus, a complementary team consisting of mental health nurse and a youth physiotherapist was recommended by the steering committee, to lead the intervention sessions. Additionally, the need to be able to rapidly address and intervene if youths experience discomfort or need adjustments to activities while still instructing the other youth, mean that at least two therapists are needed per session.

### Study population and eligibility

Youth are referred to the treatment program from their attending therapist at the local CAMHS. Youth can be included in the study if they meet the criteria below.

Inclusion criteria are as follows:Age 8–17 yearsSymptoms of anxiety and/or depressionYouth display reduced daily physical activity (less than 30 mins per day and/or does not partake in physical leisure activities, and/or does not participate in physical education in school).The youth is motivated to partake in physical activity

Exclusion criteria are as follows:Physical activity is not advised for medical reasonsSevere learning disabilities and the youth is unable to understand the study protocolSpecific psychiatric disorders including any eating disorder, psychosisSevere challenging behavior or other needs requiring constant one to one support

### Recruitment

Youth will be recruited from the CAMHS, Department of Child and Adolescent Psychiatry, Haukeland University Hospital, Norway. CAMHS is organized at the same intervention level as ordinary hospital services (Haukeland University Hospital, Bergen, Norway) and is as such a tertiary specialized service. In the Norwegian context, this is the primary source of treatment for youth with mental health disorders. CAMHS is organized in three inpatient wards, three specialized clinics, and seven outpatient clinics. These units together form the recruitment base for CAH-Y. CAMHS offers all forms of mental health services to youth in a catchment area of app. 460,000 citizens in total. The CAMHS receives approximately 3000 referrals per year and delivers treatment to 5.2% of all youth in the catchment area [37]. Taking into account CAH-Y inclusion and exclusion criteria, we estimate that 40% of these youth qualify for participation in the intervention (*n* = 600). The likely numbers of patients referred and eligible should greatly exceed the numbers required by the feasibility study, meaning well below 10% of those eligible are required to consent.

Given that CAH-Y is organized within CAMHS, this enables easy access to potential participants and streamlined recruitment strategies. In practice, this translates into the following:Uncomplicated dispersion of information regarding the intervention to the departments and mental health professionals via intranet, email and/or physical/digital meetingsEase of implementing an in-house digital referral systemA low threshold for communication between the CAH-Y team and the referring specialist

Based on the therapist’s assessment of eligibility and participant’s interest in the intervention, the therapist sends a formal referral to the CAH-Y team. The referrals are assessed with respect to inclusion/exclusion criteria by the Principal Investigator (PI is the first author). If the youth is assessed eligible, an invitation to attend a recruitment and inclusion interview is sent to the youth (and parents if the youth is below 16 years of age). Enclosed in the letter are also a number of health assessment questionnaires. The questionnaires assess mood, anxiety, demographic information, and motivation to attend the intervention. Finally, this letter informs of a webpage address, where the participant can find more information about the intervention and the study. The referring specialist will receive notification that the youth is eligible and is invited to an interview. Approximately a week prior to the interview, youth/parents are contacted via phone and they are given further information about the intervention and study participation.

### Consent

At the recruitment and inclusion interview, participants are provided further information about the intervention and the study, and any ensuing questions can be dealt with. Written information detailing the intervention, the study as well as the consent form are reviewed with the participant and/or parents if they participate in the interview. Informed written consent is obtained from all parents, and assent is obtained from youth above age 12 years. All participants in the intervention fill out the same questionnaires and go through the same assessment interview. Importantly, participation in the study requires written consent, but participation in the intervention is not dependent on participation in the study.

### Withdrawal of the study participants

At any time, participants can withdraw consent with no consequences for further intervention participation or other eventual benefits. If there are any serious adverse events, e.g., injury from the activities, details will be recorded and reported to the PI and to the work management group. CAMHS has appropriate insurance of the participants, if any adverse event should take place. In the case of adverse psychiatric effects are uncovered, this will be reported immediately to the participants referring specialist in CAMHS.

### Feasibility procedures

After referral assessment of eligibility, eligible youth and their primary caregivers are invited to attend a recruitment and inclusion interview. This interview will take place in the CAH-Y facilities. In the interview, therapists will provide further information about the intervention and study details, clarifying any questions and/or concerns, and obtaining written consent, and they collect and check the questionnaires included in the invitation for the recruitment interview. Moreover, additional questionnaires will be completed (see primary and secondary outcome measures section below), medical information gathered (height and weight), and participants will be provided an Actigraph activity monitor to be worn for the next 7 days. In addition, a short qualitative interview exploring participant and caregiver views on physical activity will be conducted. Finally, the youth and caregivers will be given a tour of the CAH-Y facilities in order to familiarize them with the setting.

The first session of the CAH-Y program will be between one to a maximum of 3 weeks after the interview. At this point, they will also return the Actigraph monitors and activity diaries. The intervention will then start. The day before every session, the participants will receive a SMS reminder of the session. After each session, participants are encouraged to visit a designated webpage for the program, where they can find further information about the next session. This is in order to remind the participants of the session clarify what is expected and encourage participation.

Following the last session of the intervention, participants will receive an invitation to attend a post-intervention interview, one to a maximum of 3 weeks following last intervention session. In this interview, questionnaires relating to symptom change will be completed, and biometric data will be gathered and a short qualitative interview exploring the views of the participant and his/her caregivers in relation to the intervention will be done. At the end of the interview, participants will be provided an Actigraph activity monitor to be worn for the next 7 days. After these seven days have elapsed, a research assistant will gather the Actigraph. Independently of this assessment with the participant, a short qualitative interview with the referring specialist will also be conducted by the PI.

At 6 months post-intervention, the participants and their caregivers will be invited to attend a follow-up interview. In this interview, questionnaires relating to initial symptoms will be completed, and a new short qualitative interview exploring views possible negative and/or positive effects of the intervention will be conducted. At the end of this interview, participants will be provided an Actigraph activity monitor to be worn for the next 7 days. After this time-period, the Actigraph will gathered by a research assistant. See Fig. 1 for study flow chart.

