### Measures

Apart from the measures that participants and their caregivers fill out at home [SCAS, SMFQ, demographics], all other measures and assessments will be conducted in the CAH-Y facilities.

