### Limitations of the research

As this is a small-scale feasibility study with no control group, it is not possible to secure blinding throughout the study. Two therapists provide the recruitment and inclusion assessment interviews and deliver the intervention. However, some of the post-intervention assessments will be done by the study PI as well as the interview with the referring specialist and follow-up interview. Whilst a double-blind feasibility design would strengthen the study, time, and resources are limited and do not allow for this. However, in the next steps of the development of the intervention (in line with the MRC Framework); including a pilot RCT and the definitive RCT, necessary personnel to avoid bias in the trial will be secured.

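### The protocol conflicts on where the symptom scales are completed; as the visit procedures are written, the setting moves from home at T1 to the interview at T2 and T3, together with treatment

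*Protocol article*

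**What the plan says.** **T1.** Under Recruitment, the invitation to the inclusion interview carries the forms: "Enclosed in the letter are also a number of health assessment questionnaires". Their content is given next: "The questionnaires assess mood, anxiety, demographic information, and motivation to attend the intervention". Under Feasibility procedures, the therapists' task with these forms at the interview is that "they collect and check the questionnaires included in the invitation for the recruitment interview". Further questionnaires are then completed on site.

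**T2.** Feasibility procedures, on the post-intervention visit: "In this interview, questionnaires relating to symptom change will be completed".

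**T3.** The same section, on the six-month visit: "In this interview, questionnaires relating to initial symptoms will be completed".

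**General statement.** The Measures section opens with "Apart from the measures that participants and their caregivers fill out at home [SCAS, SMFQ, demographics" and places every other measure in the programme facilities. It names no time point.

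**Staff.** Limitations of the research says "Two therapists provide the recruitment and inclusion assessment interviews and deliver the intervention", and that "some of the post-intervention assessments will be done by the study PI". It also assigns the follow-up interview to the PI.

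**Use of the scores.** Under Comparison group, participants are their own controls. That section, the study aims and the last paragraph of Participant-centered outcome measures all pass the pre-post effect sizes on to the planning of the definitive RCT.

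**The concern.** In a single-arm pre-post design, the change score is interpretable only if measurement conditions are the same at both ends. If a family fills in a scale at home before treatment and in a clinic interview after it, the observed change is the sum of the change in symptoms and whatever the change in setting does to the answers. Nothing in the design separates the two. In a randomised comparison the same switch would affect both arms and would largely cancel.

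Both youth and caregiver reports would be affected, so neither informant can serve as a check on the other. What is at stake is the effect-size estimate handed to the RCT. The feasibility decision is not at stake.

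**Working it through.** The point is procedural. The target of 20 participants has no alpha, power, effect size or SD behind it, so there is no stated figure to reproduce.

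**Step 1. Completion setting by time point**

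| Time point | Visit procedures (Recruitment, Feasibility procedures) | Measures section, read literally | Measures section, read as baseline only |
|---|---|---|---|
| T1 | Mailed beforehand; collected and checked at interview | Home | Home |
| T2 | Completed in the interview | Home | Not addressed |
| T3 | Completed in the interview | Home | Not addressed |

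The T1 text distinguishes mailed forms that are handed in from additional ones completed on site. The T2 and T3 text uses only the on-site wording for symptom forms and mentions nothing sent out or collected. Taken by visit, the setting therefore changes between T1 and T2.

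**Step 2. Can the Measures section be reconciled with this?**

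- If it covers all visits, it contradicts the T2 and T3 procedures. The scales would be done at home throughout, and there would be no change of setting.
- If it means baseline only, there is no contradiction, but the change of setting is real. Its at-home list includes demographics, which Table 1 schedules at T1 only. That favours this reading, but the section does not say so.

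Either the text contradicts itself or the setting changes with treatment. A related mismatch is that Recruitment mails a motivation questionnaire, while the at-home list in Measures leaves it out.

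**Step 3. What a shift would do to RCT planning (illustration; every input is assumed)**

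Assume two-sided alpha 0.05, power 80%, 1:1 allocation and SD 1, and suppose the pre-post d is carried straight over as the between-arm d. The per-arm size is n = 2(1.96 + 0.84)² / d², rounded up. Power at the true d is Φ(d·√(n/2) − 1.96). A setting shift of s, in the same SD units, turns a true d into d + s.

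| True d (n per arm) | Shift s | Apparent d | Planned n per arm | Power at true d |
|---|---|---|---|---|
| 0.5 (63) | +0.1 | 0.6 | 44 | 65% |
| 0.5 (63) | +0.2 | 0.7 | 33 | 53% |
| 0.5 (63) | −0.1 | 0.4 | 99 | 94% |
| 0.5 (63) | −0.2 | 0.3 | 175 | 99.7% |
| 0.3 (175) | +0.1 | 0.4 | 99 | 56% |
| 0.3 (175) | +0.2 | 0.5 | 63 | 39% |
| 0.3 (175) | −0.1 | 0.2 | 393 | 98.8% |
| 0.3 (175) | −0.2 | 0.1 | 1570 | over 99.9% |

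Worked line: with s = +0.1 and true d = 0.5, n = 2(2.80)²/0.36 ≈ 43.6, so 44. Power is Φ(0.5·√22 − 1.96) = Φ(0.385) = 65%.

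**Step 4. Compared with sampling error**

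For a standardised pre-post change, SE ≈ √(1/n + d²/(2n)). With n = 20 and d = 0.3, the 95% half-width is 1.96·√(0.05 + 0.00225) ≈ 0.45; with d = 0.5 it is 0.46. A shift of 0.1 to 0.2 lies well inside that. It is nevertheless a bias: the interval does not show it, and more participants would not remove it.

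**The case against.** The strongest reply is that the change of setting is not established. Measures puts SCAS and SMFQ at home without restriction, and the T2 and T3 sentences may be loose wording in a condensed article; they do not even name the instruments. This stands in part: the switch cannot be stated as fact. It does not remove the point, because the text then contradicts itself on how the main symptom outcomes are collected.

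A reader might also infer that families answer in front of the people who treated them and so report fewer symptoms. The documents do not support that. No section says who is present when the forms are filled in, or that staff administer them. The PI, who does the follow-up interview and part of the T2 assessments, is not described as delivering sessions. Programme staff also check the forms at T1. The direction of any shift is therefore open.

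Third, the consequences are limited. None of the three progression criteria (adverse events, recruitment, retention) uses a symptom score. The statistics section treats the quantitative results as feasibility and pilot data only, and the limitations already concede the absence of a control group and blinding. An uncontrolled change on top of ongoing treatment is a weak planning input in any case. All of this is fair. But the protocol still sends these effect sizes to the RCT power calculation, and a change of setting, unlike the missing control group, can be avoided at little cost.

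**Conclusion.** The point holds in a limited form. The visit procedures and the Measures section disagree about where SCAS and SMFQ are completed at T2 and T3. If the visit procedures are followed, setting changes together with treatment, and any effect of that change is inseparable from the pre-post effect size.

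The size is unknown. It might be tempting to express the bias as a percentage of the expected effect, but that would only divide one assumption by another: the documents give no shift, no expected effect and no direction. The sample-size table shows how sensitive RCT planning is to shifts of 0.1 to 0.2 SD either way; it does not estimate what will happen. Decisions on progression are unaffected. This is worth correcting because the remedy is cheap. It does not undermine the feasibility aims.

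**What to change.** State for each of T1, T2 and T3 where SCAS-C/P and SMFQ-C/P are completed, and use the same mode every time. Do the same for the motivation form mailed at T1. The simplest route is to enclose the forms with the T2 and T3 invitations, have them completed at home, and collect and check them at the visit as at T1. Align Recruitment, Feasibility procedures and Measures accordingly, including the motivation form missing from the at-home list.

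Record the place of completion for every form. For participants already assessed in the interview, report the mode difference as a limitation of the effect-size estimate. Splitting the change by setting will not rescue it: if every T1 form was done at home and every T2 form in the interview, setting and time are fully confounded.

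The cost is small, since families are already invited to both visits. There are two downsides. Some forms will come back incomplete or not at all, and will have to be completed at the visit and flagged. And because inclusion has been under way since April 2020, a change now may mix modes among about 20 participants, which should be stated alongside the results.
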